### Participant timeline

Step1: Patients meeting the selection criteria would be approached to participate in the study. A written informed consent would be obtained as approved by the ethics committees, after describing the study procedures with video aids. All treatments would be added to ongoing pharmacotherapy. In step-1, Participants would be randomised to either of the groups to receive “cTBS with sham-tDCS” or “active tDCS with sham TBS” twice a day for 15 days (over 3 weeks).

Step-2:

Upon non-response to step-1, participants would cross over to the other set of interventions in step-2 after a wash-out period of 2–4 weeks. Participants with <30% improvement in AHRS from baseline at the end of 2–4 weeks of the trial would be considered non-responders for inclusion to Step-2. Written informed consent would again be obtained before the initiation of step 2.

The order of TBS and tDCS would be maintained as was delivered in step-1 for the given participant (See
Figure 2).

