**Methods:**

Two hundred and ten consenting patients with schizophrenia with persistent auditory hallucinations will be randomly assigned to receive 15 days (30 sessions) of c-tDCS+sham-TBS or sham-tDCS+cTBS over the left temporoparietal region at three study centres. After a gap of 2-4 weeks, non-responders to the intervention will cross-over to the other arm. Clinical assessments, neurocognitive assessments, and multimodal investigations (magnetic resonance imaging, electroencephalography, heart rate variability, investigative transcranial magnetic stimulation-transcranial direct current stimulation, gene polymorphisms) will be conducted at baseline and repeated after the end of both phases of the trial. A differential pre-treatment resting brain functional connectivity signal will identify responders to cTBS or c-tDCS.

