### Aims and hypothesis

**
*Primary*
**

To identify resting brain functional connectivity markers of response to continuous Theta Burst Stimulation (cTBS) and cathodal transcranial Direct Current Stimulation (c-tDCS) in patients with schizophrenia with persistent auditory hallucinations to improve the efficacy of interventions.Hypothesis: A differential pre-treatment resting brain functional connectivity signal will identify responders to cTBS or c-tDCS

**
*Secondary*
**

To compare the neurobiological profile of patients with schizophrenia with persistent auditory hallucinations with matched healthy controls using multi-modal data [brain imaging, Electroencephalography (EEG), TMS-tDCS perturbation study metrics, Heart Rate Variability (HRV), and neuroplastic gene polymorphisms].To examine the differential effect of cTBS versus c-tDCS on the neurobiological profile of patients with schizophrenia with persistent auditory hallucinations using multi-modal data (brain imaging, EEG, TMS-tDCS perturbation study metrics, HRV) and potential interactions with neuroplasticity gene polymorphisms.To evaluate the predictive utility of multi-modal data (brain imaging, EEG, TMS-tDCS perturbation study metrics, HRV, and neuroplastic gene polymorphisms) in identifying clinical response to cTBS or c-tDCS in patients with schizophrenia with persistent auditory hallucinations.

This study protocol adheres to the SPIRIT guidelines (
[name] *et al.*, 2023) and the example consent form and study proforma can be found as
*Extended data* (
[name] *et al.*, 2023).

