Secondary outcome measures include broader clinical symptoms, adverse effects, and neurobiological parameters (The detailed protocol of neurobiological parameters will be described in a separate paper). Clinical symptoms would be measured by the auditory hallucinations rating scale (AHRS) (
Haddock *et al.*, 1999), Scale for assessment of positive symptoms (SAPS) and negative symptoms (SANS) (
Andreasen, 1983;
Andreasen, 1984), Calgary Depression Scale for Schizophrenia (CDSS) (
Addington *et al.*, 1994), Clinical Global Impressions (CGI) and Montreal Cognitive Assessment (MoCA) (
Nasreddine *et al.*, 2005) will be applied at baseline and every week till the end of the intervention. Cognitive and functional abilities will be assessed using the Brief Assessment of Cognition in Schizophrenia (BACS) (
Keefe *et al.*, 2004), Groningen Social Disability Schedule (GSDS) (
Wiersma *et al.*, 1988) and social and occupational functioning scale (SOFAS) (
Morosini *et al.*, 2000) at baseline and after each step of intervention.

Safety of the intervention sessions will be another secondary outcome measure: the tDCS-related adverse effect questionnaire Field (
Brunoni *et al.*, 2011;
Chhabra *et al.*, 2020) and the TMS-related adverse effects questionnaire Field (
Giustiniani *et al.*, 2022) will be used to monitor adverse effects after each intervention session.

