**Figure 2. f2:**
[figure not shown]
Depiction of the study procedure. In the first step of the study, the patients with persistent auditory verbal hallucinations would be randomized to receive 15 days of cTBS+sham-tDCS or sham TBS+active tDCS. Patients with clinical non-response even after 2–4 weeks of the end of the trial will be cross-covered to receive 15 days of the other set of interventions. Neuroimaging, and neurophysiological tests would be done before initiating and after the end of intervention with each step. Blood samples would be collected for genetic polymorphism assays at the baseline. Blue stars depict the time points of symptom rating and multimodal data acquisition. SZ: Schizophrenia, tDCS: transcranial direct current stimulation, cTBS: continuous theta burst stimulation, TMS: Transcranial Magnetic Stimulation, MRI: Magnetic resonance imaging, EEG: Electroencephalogram, TMS/tDCS: Transcranial magnetic stimulation/transcranial direct current stimulation, BDNF: Brain-derived neurotrophic factor, COMT: Catechol-O-methyltransferase.

**
*Sample size*
**

In order to identify a clinically relevant and appropriately corrected statistically significant signal from resting-state brain connectivity data with sufficient (~80%) power to differentiate (P<0.05) groups of responders and non-responders, a sample size ranging from 27 to 32 has been recommended for each group (
Pajula & Tohka, 2016;
Thirion *et al.*, 2007;
Zandbelt *et al.*, 2008) and similar sample size has shown utility in studies attempting to predict response (
Khalili-Mahani *et al.*, 2017;
Martens *et al.*, 2022;
Parlikar *et al.*, 2023;
Zhang *et al.*, 2022). Keeping with this, we will recruit 210 participants who will be randomized in part-1 of the treatment. Anticipating ~15% dropout, we will have ~180 participants who will complete the part-1 treatment. Assuming a third of the participants respond to either treatment arm, a sample of 60 and 120 will be categorised as responders and non-responders, respectively. We expect at least three-quarters of the non-responders to consent to the crossover treatment. Given our experience in a previous trial (

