Personality assessment	Mini International Personality Item Pool (Mini- IPIP)	Baseline
Depressive symptoms	Calgary Depression Rating Scale	Screening/Baseline, post-step-1, pre step-1 and post-step-2
Neurocognitive assessment	Montreal Cognitive assessment (MoCA)	Baseline and weekly during the trial period
Neurocognitive assessment	Brief Assessment of Cognition in Schizophrenia (BACS)	Baseline, post-step-1, pre-step-2 and post-step-2
Auditory hallucinations	Auditory hallucinations rating scale (AHRS), Mental Health Research Institute Unusual Perceptions Schedule (MUPS)	Baseline and weekly during the trial period
Positive symptoms	Scale for the Assessment of Positive Symptom Scale (SAPS)	Baseline and weekly during the trial period
Negative symptoms	Scale for the Assessment of Negative Symptoms (SANS)	Baseline and weekly during the trial period
General psychopathology	Brief psychiatric rating scale (BPRS)	Screening/Baseline and weekly during the trial period
tDCS and TMS side effects	TMS-related adverse effects questionnaire and tDCS related adverse effect questionnaire	After each session of tDCS and iTBS
Disability and functioning	Groningen Social Disability Schedule (GSDS)	Baseline, post-step-1, pre-step-2 and post-step-2
Functional ability	Social and occupational functioning scale (SOFAS)	Baseline, post-step-1, pre-step-2 and post-step-2
Global clinical severity	Clinician Global Impression-severity (CGI-S)	Baseline, post-step-1, pre-step-2 and post-step-2
Neurobiological tests	MRI/MRS/EEG/Perturbation tests/HRV	Baseline, post-step-1, pre-step-2 and post-step-2
Genotyping	Blood sampling	Baseline

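### The only response criterion is timed inconsistently and, even on the likely reading, has no fixed visit, although the primary hypothesis and the sample-size groups rest on responder status

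*Protocol article*

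**What the plan says.** - **Criterion.** Participant timeline, Step-2: "Participants with <30% improvement in AHRS from baseline at the end of 2–4 weeks of the trial would be considered non-responders". The sentence attaches this to entry into Step-2. No other definition of response appears in the article.
- **Timing in the Figure 2 legend.** "Patients with clinical non-response even after 2–4 weeks of the end of the trial will be cross-covered".
- **Wash-out.** Participant timeline, Step-2, in the sentence before the criterion: "participants would cross over to the other set of interventions in step-2 after a wash-out period of 2–4 weeks". The abstract's Methods agree: "After a gap of 2-4 weeks, non-responders to the intervention will cross-over to the other arm".
- **Length of step 1.** Participant timeline, Step1: "twice a day for 15 days (over 3 weeks").
- **AHRS schedule.** The secondary-outcome text says that the clinical scales, AHRS among them, "will be applied at baseline and every week till the end of the intervention". Table 1 gives AHRS as "Baseline and weekly during the trial period". For BACS, GSDS, SOFAS and CGI-S, Table 1 names post-step-1, pre-step-2 and post-step-2 explicitly. Trial procedures and evaluations says that clinical evaluations are repeated before and after each step.
- **Use of responder status.** The primary hypothesis in Aims and hypothesis reads "A differential pre-treatment resting brain functional connectivity signal will identify responders to cTBS or c-tDCS". The Sample size section powers a comparison of responders with non-responders and expects 60 and 120 of them among about 180 completers.

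**The concern.** Responder status is what the primary hypothesis sets out to predict, and it forms the groups in the sample-size argument. It also decides who may enter step 2, so the rule operates during the trial and cannot wait for an analysis plan. The criterion's percentage threshold is fixed but its date is not. A patient whose AHRS change crosses 30% between two permissible dates is a responder on one and a non-responder on the other. The label would then mix acute response, durable response and relapse during wash-out, in proportions that depend on when each patient or site happened to rate. Labels assigned in this way tend to blur any association between connectivity and response.

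**Working it through.** **1. The plan's own figures.** The sample-size chain reproduces.
- Completers: 210 × 0.85 = 178.5, stated as about 180.
- Responders: 180 / 3 = 60. Non-responders: 180 − 60 = 120.
- Crossing over: 0.75 × 120 = 90.
- Responders per arm: 60 / 2 = 30, matching the stated minimum of about 30 per group.

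There is no arithmetic error. Every figure from 60 onward, however, depends on when response is judged.

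**2. The two timings on one scale.** Day 0 is the start of step 1, and treatment ends about day 21 (three weeks).

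| Source | Literal meaning | Days |
|---|---|---|
| Participant timeline, Step-2 | 2–4 weeks of the trial | 14–28 |
| Figure 2 legend | 2–4 weeks after its end | 21 + 14 = 35 to 21 + 28 = 49 |

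The first window opens about a week before treatment is complete. The windows are 35 − 28 = 7 days apart at the closest and 49 − 14 = 35 days at the widest. Each is 14 days wide, with no rule for choosing the date inside it.

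**3. Which reading is likely.** The abstract and the wash-out sentence both place the 2–4 weeks after step 1. The Figure 2 legend does the same and uses the word trial for the step-1 course. The Step-2 criterion is therefore probably a loose description of the same gap. The 14-day float then remains.

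**4. Is a rating scheduled there?** The Outcome text stops AHRS at the end of the intervention. Table 1 has it weekly during the trial period and does not name pre-step-2, although it does so for other scales. Trial procedures and evaluations implies a clinical evaluation before step 2. Figures 2 and 3 may mark the time point but are not available here. A pre-step-2 AHRS rating is plausibly planned but is not named.

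**5. Illustration of relabelling between two dates.** Assumptions: one third respond at each date (the plan's rate, applied to both); AHRS change at the two dates is bivariate normal with correlation ρ. No value of ρ is given in the documents.

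Proportion changing label = 2 × (1/3 − P), where P is the probability of responding at both dates. The share of responders at one date who are non-responders at the other is 1 − 3P.

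| ρ | P | Change label | Of 180 | Responders at one date who are non-responders at the other |
|---|---|---|---|---|
| 0.7 | 0.219 | 23.0% | 41 | 34% |
| 0.8 | 0.240 | 18.6% | 33 | 28% |
| 0.9 | 0.268 | 13.1% | 24 | 20% |

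Percentages and counts are from unrounded P.

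**The case against.** The best defence is that this is a drafting slip. Three places put the 2–4 weeks after treatment, and judging non-response in week 2 of a three-week course fits poorly with crossing over upon non-response to step 1. That stands, and it removes most of the force of the literal contradiction. It does not supply a fixed date.

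Several stronger readings are tempting but not supported:

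- **That no AHRS rating exists at the judgement date.** The statement that clinical evaluations are repeated before and after each step points the other way, and the two schedule figures cannot be seen. Only the lack of an explicit entry can be claimed.
- **That step 1 and step 2 necessarily have different endpoints.** AHRS is weekly to the end of the intervention, so an end-of-course value should exist in both steps. Nothing says that the analysis label must be read after wash-out.
- **That the crossover criterion is declared to be the analysis definition.** It is stated for Step-2 entry. Using it as the analysis label is an inference, though a reasonable one because no other definition is given. A fuller document may hold one.
- **That the primary outcome itself is undefined.** As worded under Outcome, it is the differential change in connectivity between arms, which does not use responder status. The hypothesis and the sample size do.
- **That 13–23% of patients would be mislabelled.** That range compares two dates, of which probably only one is intended, under an assumed correlation. Within a single 14-day window the correlation could be higher and the switching lower.

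Blinding of assessors and investigators to arm limits the scope for choosing a date in favour of one treatment. It does not make the date the same for every patient.

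**Conclusion.** The point holds in limited form. The response criterion is given two literal timings that do not overlap. On the likely reading, both mean the post-treatment gap, but the date is still a two-week range with no fixed visit, and AHRS is not named at pre-step-2. The label behind the primary hypothesis and the powered groups can therefore depend on when a patient is rated.

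The figure of 24–41 of 180 changing label shows how sensitive the label could be. It rests on one third responding at each date and on an assumed correlation of 0.7–0.9, so it does not measure an error in this trial. The stated sample-size figures reproduce, and this point alone does not call for a change to the 210. Severity: should fix.

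**What to change.** 1. **Analysis definition.** Define response for analysis at one fixed visit, used identically in step 1 and step 2, and state the reference rating for each step. The end-of-course post-step visit is one example: weekly AHRS and the post-step scan are already scheduled there.
2. **Post-wash-out rating.** Report the post-wash-out AHRS as a separate outcome at one fixed week, and list AHRS explicitly at pre-step-2 in both the Outcome text and Table 1.
3. **Crossover wording.** The trial team must reconcile the abstract, the Step-2 criterion and the Figure 2 legend, and keep crossover eligibility distinct from the analysis definition. No crossover rule is proposed here.

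The cost is a wording amendment and, if not already planned, one AHRS rating at the existing pre-step-2 assessment. One drawback is that some patients who count as responders for analysis may relapse in wash-out and still qualify to cross over. Their number should be reported.

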**Figure 2. f2:**
[figure not shown]
Depiction of the study procedure. In the first step of the study, the patients with persistent auditory verbal hallucinations would be randomized to receive 15 days of cTBS+sham-tDCS or sham TBS+active tDCS. Patients with clinical non-response even after 2–4 weeks of the end of the trial will be cross-covered to receive 15 days of the other set of interventions. Neuroimaging, and neurophysiological tests would be done before initiating and after the end of intervention with each step. Blood samples would be collected for genetic polymorphism assays at the baseline. Blue stars depict the time points of symptom rating and multimodal data acquisition. SZ: Schizophrenia, tDCS: transcranial direct current stimulation, cTBS: continuous theta burst stimulation, TMS: Transcranial Magnetic Stimulation, MRI: Magnetic resonance imaging, EEG: Electroencephalogram, TMS/tDCS: Transcranial magnetic stimulation/transcranial direct current stimulation, BDNF: Brain-derived neurotrophic factor, COMT: Catechol-O-methyltransferase.

**
*Sample size*
**

In order to identify a clinically relevant and appropriately corrected statistically significant signal from resting-state brain connectivity data with sufficient (~80%) power to differentiate (P<0.05) groups of responders and non-responders, a sample size ranging from 27 to 32 has been recommended for each group (
Pajula & Tohka, 2016;
Thirion *et al.*, 2007;
Zandbelt *et al.*, 2008) and similar sample size has shown utility in studies attempting to predict response (
Khalili-Mahani *et al.*, 2017;
Martens *et al.*, 2022;
Parlikar *et al.*, 2023;
Zhang *et al.*, 2022). Keeping with this, we will recruit 210 participants who will be randomized in part-1 of the treatment. Anticipating ~15% dropout, we will have ~180 participants who will complete the part-1 treatment. Assuming a third of the participants respond to either treatment arm, a sample of 60 and 120 will be categorised as responders and non-responders, respectively. We expect at least three-quarters of the non-responders to consent to the crossover treatment. Given our experience in a previous trial (
Bose *et al.*, 2018), this will result in about 90 participants receiving the crossover treatment in part-2. A sample of 210 recruited at baseline will provide us with a minimal sample of ~30 participants in each group to permit sufficiently powered statistical inference about resting-state brain connectivity determinants of treatment response. Appropriate statistical modelling will be performed to delineate resting brain connectivity networks to identify general and specific response signals to cTBS and c-tDCS. For comparison studies between patients and healthy controls, a sample size of at least 210 healthy subjects will offer optimal power as per the sample size of previous neurobiological studies in this area.

### Allocation

**
*Sequence generation*
**

Consenting patients would be randomly assigned using computer-generated codes to true/sham interventions. Random allocation of 2 treatments (iTBS+sham-tDCS and active tDCS+sham-TBS) for 3 study centres with unequal strata sizes of 126, 42 and 42 would be carried out in Stata Statistical Software release.15.1 (College Station, TX: StataCorp LLC). This procedure would provide a sequence list, which would be randomly permuted in blocks of varying sizes and order. An independent statistician would manage the randomisation and allocation concealment. The allocation sequence generation is centrally coordinated at NIMHANS.

**
*Concealment mechanism*
**

Allocation concealment would be ensured through sequentially numbered sealed opaque envelopes.

**
*Blinding (masking)*
**

The participants, their caregivers, investigators, safety assessors, outcome assessors, treating psychiatrists, data managers, and data analysts would be blinded to the allocated study arm.

**
*Emergency unblinding*
**

Serious adverse events (SAE) would be reported to the trial management group (TMG) by the site investigator, and the principal investigator would thereafter report it to the data and safety monitoring board (DSMB), which would assess for suspected unexpected serious adverse reaction (SUSAR); the patient, caregiver, clinical team, and the investigators may be unblinded at their discretion. Assessment of blinding efficacy would be done on patients and outcome assessors after the last (scheduled/terminated) day of intervention with each step using a 5-point Likert scale.

**
*Trial procedures and evaluations*
**

In addition to the above-discussed screening and outcome tools, all participants would be assessed using a comprehensive semi-structured proforma to collect the socio-demographic and clinical details. Mental health professionals would perform clinical ratings. They would be trained in administering the clinical rating scales, and inter-rater reliability assessments would be performed for outcome measures. Comprehensive data collection forms would be available with the investigators and would be made available on reasonable request.

Multi-modal neurophysiological data (magnetic resonance imaging, EEG, cortical perturbation using transcranial magnetic stimulation- transcranial direct current stimulation, heart rate variability) would be acquired before and after interventions to identify predictive factors and understand the mechanistic basis of the treatment outcomes.

MRI data will be acquired in a 3T scanner (Ingenia CX, Philips). Structural MRI: T1-weighted single-shot 3D turbo field echo image.TR=2500-ms; TE=2.9-msec; FOV=256-mm; slice-thickness=1-mm; Matrix=256*256; Voxel size= 1*1*1-mm. Resting-state fMRI (RS-fMRI): Participants will be instructed to relax, not think anything actively, and lay still with their eyes open. The scan will be acquired with the following parameters: TR=2200 ms; TE=28-ms; slice-thickness=3mm; slice-number=44; Gap=0.3mm; Matrix=64*64*64; voxel=3.0-mm isotropic with 275-dynamic scans that lasts for 10 minutes and 20 seconds.

Clinical and neurobiological evaluations would be repeated before and after each intervention step (Detailed in
Table 1 and
Figure 3). Also, neuroplasticity gene polymorphisms (Brain-derived neurotrophic factor (BDNF) and catechol-O-methyltransferase (COMT) genes) will be assessed alongside clinical and neurophysiological data to identify the predictors of clinical response. At least 300 subjects matched (as a group) for age, sex, education, handedness, and socio-economic status would be chosen for the comparative analyses of neurobiological studies. They would undergo a one-time baseline assessment of clinical and neurobiological parameters. The details of the neurobiological data acquisition protocol will be described in a separate paper.

**Table 1. T1:** Scheduled Clinical assessments in the study.

Clinical Measure	Clinical Measurement tool	Timeline
Diagnosis	Structured clinical interview for DSM-5 disorders, clinician version (SCID-CV)	Screening
Handedness	Edinburgh handedness scale	Screening
Capacity to consent to participate in the research	University of California, San Diego Brief Assessment of Capacity to Consent (UBACC)	Screening and Pre-step-2
Safety screening for Transcranial magnetic stimulation (TMS)	TMS Adult safety screen (TASS)	Screening
Safety for magnetic resonance imaging (MRI)	MRI-safety checklist	Screening
Clinical details	Comprehensive semi-structured proforma	Screening/Baseline
Global response to each of past antipsychotic trials	Clinical global impression-improvement	Screening/Baseline
Personality assessment	Mini International Personality Item Pool (Mini- IPIP)	Baseline
Depressive symptoms	Calgary Depression Rating Scale	Screening/Baseline, post-step-1, pre step-1 and post-step-2
Neurocognitive assessment	Montreal Cognitive assessment (MoCA)	Baseline and weekly during the trial period
Neurocognitive assessment	Brief Assessment of Cognition in Schizophrenia (BACS)	Baseline, post-step-1, pre-step-2 and post-step-2
Auditory hallucinations	Auditory hallucinations rating scale (AHRS), Mental Health Research Institute Unusual Perceptions Schedule (MUPS)	Baseline and weekly during the trial period
Positive symptoms	Scale for the Assessment of Positive Symptom Scale (SAPS)	Baseline and weekly during the trial period
Negative symptoms	Scale for the Assessment of Negative Symptoms (SANS)	Baseline and weekly during the trial period
General psychopathology	Brief psychiatric rating scale (BPRS)	Screening/Baseline and weekly during the trial period
tDCS and TMS side effects	TMS-related adverse effects questionnaire and tDCS related adverse effect questionnaire	After each session of tDCS and iTBS
Disability and functioning	Groningen Social Disability Schedule (GSDS)	Baseline, post-step-1, pre-step-2 and post-step-2
Functional ability	Social and occupational functioning scale (SOFAS)	Baseline, post-step-1, pre-step-2 and post-step-2
Global clinical severity	Clinician Global Impression-severity (CGI-S)	Baseline, post-step-1, pre-step-2 and post-step-2
Neurobiological tests	MRI/MRS/EEG/Perturbation tests/HRV	Baseline, post-step-1, pre-step-2 and post-step-2
Genotyping	Blood sampling	Baseline

